#### Economic analysis

The purpose of the economic evaluation is to examine the incremental cost-effectiveness of SLT relative to medical care. Costs will be quantified from the health system perspective using an activity based costing approach. Sunk costs will be excluded from the analysis. Effectiveness will be defined in terms of the AQoL-7D utilities. Once costs and effectiveness are known for each intervention arm at both baseline and follow-up, the approach for quantifying cost-effectiveness will follow that described in the literature [46]. As is common practice, incremental cost-effectiveness ratios will be compared with common thresholds adopted by National Institute for Health and Care Excellence (NICE) and World Health Organisation (WHO) for what represents good value for money. In addition to quantifying this ratio, we will also conduct one-way and n-way sensitivity analyses and produce cost effectiveness acceptability curves (CEAC) to show the probability that SLT is cost-effective for a range of monetary values that a decision-maker might be willing to pay for a unit change in quality adjusted life year (QALYs). Finally, because much of the costs of SLT are one-time fixed costs, and topical medication(s) is a recurring cost, if the results show SLT to be at least as effective as topical medication, the average time it takes for SLT to become a dominant strategy will also be quantified. All analyses will be conducted using TreeAge software.

#### Clinical efficacy

To assess clinical efficacy (IOP reduction success), Chi square tests will be used and multivariable logistic regression models with odds ratios (OR) and 95 % CI will be built. Other analyses will be tailored to the nature of the secondary outcome data. Numerical data (for example, IOP and visual acuity) and dichotomous data (presence/absence) will be analysed by the GEE. Survival data (for example, time-to-VF (visual field) progression, IOP becoming uncontrolled again) will be analysed using survival analysis. Stepwise multiple regression analyses for secondary outcomes will evaluate a similar set of potential explanatory factors (covariates) in addition to treatment assignment and those evaluated for the primary analysis. Time-varying covariates will be used for analyses evaluating repeated measures of the outcome, if appropriate. Standard errors of estimates from log-linear models will take account of possible over-dispersion with respect to the assumed models.

To determine the impact of SLT (single or multiple applications) on safety, surgical complications, and common side effects associated with glaucoma treatment, Chi square tests will be used initially and regression models with ORs and 95 % CI will be built. Where appropriate, Poisson regression will be used to compare event rates (for example, adverse events). To determine the predictors of IOP reduction success, survival curves will be constructed using the Kaplan-Meier method. Cox proportional hazards method will be used to adjust for confounders. Hazard ratios (HR) with 95 % CI will be provided to estimate the relative risk.

### Planned subgroup analyses

Analyses for the primary (HRQoL) and secondary outcomes (clinical efficacy) will be stratified for baseline types of glaucoma (POAG and XFG).

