**Methods/Design:**

This protocol describes an international, multi-centre, randomised controlled trial to determine the optimum first-line therapy for people with primary open-angle glaucoma and exfoliative glaucoma. This study will compare the effect of selective laser trabeculoplasty and topical medication with respect to patients’ generic and glaucoma-specific quality of life. The trial will also provide a detailed cost-effectiveness analysis and compare the clinical effectiveness with respect to the degree of intraocular pressure lowering and rates of treatment failure. Research coordinators in each centre will identify and recruit previously untreated patients with primary open-angle glaucoma and exfoliative glaucoma. Those who meet the eligibility criteria will be invited to enter a randomised controlled trial with either selective laser trabeculoplasty or topical ocular hypotensive therapy, according to a stepped regimen. Outcome assessment will be measured at 6 weeks and at 6, 12, and 24 months post-treatment. Regular clinic follow-ups will continue as clinically indicated between study outcome visits.

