### Interventions

Patients will be randomised 1:1 to treatment with either SLT or topical ocular hypotensive therapy, according to a stepped regimen (Figs. 1 and 2). If both eyes meet the inclusion criteria, the eye with the highest IOP will be enrolled in the study. However, both eyes will receive the same treatment initially. If both eyes have the same level of IOP, it will be at the investigator’s discretion to choose the study eye based on visual fields and optic disc evaluation.

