### Statistical analysis plan

All data analyses will be conducted according to a pre-specified analytical plan using Stata version 12.1.0 (Stata Corp, College Station, TX). All hypothesis testing will be performed at the 5 % two-sided significance level. Analyses and data summaries will be carried out using the intention to treat (ITT) population. The ITT population is defined as all patients registered for active follow-up regardless of non-adherence with the intervention. All patients will be analysed according to the intervention that they were randomised to. A per-protocol analysis will be considered if there are a considerable number of protocol violators.

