### Sample size estimation

The sample size for the study is based on the primary outcome measure of HRQoL at 24 months post-treatment. Our hypothesis is that compared with topical medication, SLT treatment will have a significantly greater positive impact on HRQoL. Mean and standard deviations for the pilot data of GOAT and previous work with the Glau-QoL were used [36, 38]. To detect a 0.156 Logit difference (effect size of 0.3) on the Rasch-analysed GOAT and Glau-QoL at 80 % power with a 5 % level of significance, 175 patients will be needed in each group. Similarly, the mean and standard deviation values for the AQoL-7D were obtained from the literature [39, 47]. To detect a 0.7 difference (effect size of 0.3) on the AQoL-7D between the two groups at 24 months with 80 % power at 5 % level of significance; 176 patients will be needed for each group. Assuming an attrition rate of 15 % after 2 years, 193 patients will be enrolled in each group at baseline. Furthermore, for Aim 3, the study will also have 79 % power to detect a 10 % difference in ‘success rate’ of IOP (defined as ≥25 % reduction in baseline IOP) in the SLT group compared with topical medication using a two-sided log-rank test at the 5 % significance level.

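### The planned analysis by glaucoma type gives results within POAG and within XFG, but no contrast that shows whether the treatment effect differs between them

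*Protocol article*

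**What the plan says.** The section *Planned subgroup analyses* consists of this sentence: "Analyses for the primary (HRQoL) and secondary outcomes (clinical efficacy) will be stratified for baseline types of glaucoma (POAG and XFG"). It covers the HRQoL and clinical efficacy outcomes; economic and safety outcomes are not named.

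The *Primary analysis* section plans GEE or GLMM regressions for HRQoL. The *Clinical efficacy* section lists chi-square tests, logistic regression, GEE and survival models. Neither names a treatment-by-type term. The *Statistical analysis plan* section adds that "All hypothesis testing will be performed at the 5 % two-sided significance level". A Bonferroni adjustment is mentioned for the multiple regression models, without the number of tests and without reference to subgroups.

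The *Randomisation* section makes type of glaucoma a stratification factor. The sample size is set for the whole trial: "175 patients will be needed in each group" for the GOAT and Glau-QoL, and "176 patients will be needed for each group" for the AQoL-7D. No XFG share and no subgroup power are given.

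**The concern.** The abstract says the trial is meant "to determine the optimum first-line therapy for people with primary open-angle glaucoma and exfoliative glaucoma". A reader of the results will therefore ask whether the answer is the same for both types. Two within-type analyses do not address that. Each has the null hypothesis of no effect in its own type, whereas the subgroup question has the null hypothesis of equal effects.

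The trial is sized for the whole sample, so each type on its own has less power, and the smaller type has least. A significant result in POAG beside a non-significant one in XFG would be likely even if both types responded identically. It could be read as benefit in one type only, and the stated analysis contains nothing to check that reading.

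**Working it through.** **Inputs from the article.** Effect size 0.3 SD (0.156 logit, so SD = 0.156 / 0.3 = 0.52); 80 % power; two-sided 5 %; 1:1 allocation; 175 per arm needed; 193 per arm enrolled with 15 % attrition, so 193 × 0.85 = 164 evaluable per arm. Randomisation is stratified by type, so the arms are about equal within each type.

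**Assumption.** XFG share f, which the article does not give: mainly 10-30 %, with 5 % and 50 % as outer values.

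**The plan's own figure.** n = 2(1.960 + 0.842)² / 0.3² = 174.4, so 175 per arm. The t-test version gives 175.4, so 176. Both stated figures are reproduced.

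**Power within each type, same true effect of 0.3 SD in both.** With m patients per arm in a type, power = Φ(0.3√(m/2) − 1.96) + Φ(−0.3√(m/2) − 1.96). For f = 10 % and 164 per arm:
- POAG: m = 147.6; 0.3√73.8 = 2.577; power = Φ(0.617) = 73 %.
- XFG: m = 16.4; 0.3√8.2 = 0.859; power = Φ(−1.101) + Φ(−2.819) = 14 %.

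**Chance that exactly one type is significant.** The two types contain different patients, so the estimates are independent and the probability is pP(1 − pX) + pX(1 − pP). For f = 10 % this is 0.731 × 0.862 + 0.138 × 0.269 = 0.67.

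| XFG share | Power POAG | Power XFG | Exactly one significant |
|---|---|---|---|
| 5 % | 75 % | 9 % | 71 % |
| 10 % | 73 % | 14 % | 67 % |
| 20 % | 68 % | 23 % | 60 % |
| 30 % | 62 % | 32 % | 55 % |
| 50 % | 48 % | 48 % | 50 % |

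A test of the treatment-by-type interaction rejects in 5 % of such trials by construction. Simulation of 200,000 pairs of estimates at shares of 10, 20 and 30 % gave 5.1, 5.1 and 5.0 %, and the same discordance of 67, 60 and 55 %.

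**How far this depends on the assumptions.** Discordance with 175 per arm and XFG shares of 5, 10, 20, 30 and 50 %:

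| True effect in both types | 5 % | 10 % | 20 % | 30 % | 50 % |
|---|---|---|---|---|---|
| 0.5 SD | 82 % | 68 % | 45 % | 28 % | 16 % |
| 0.3 SD | 73 % | 68 % | 61 % | 55 % | 50 % |
| 0.2 SD | 45 % | 44 % | 42 % | 40 % | 39 % |
| 0.1 SD | 19 % | 19 % | 19 % | 18 % | 18 % |

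With no effect in either type it is 2 × 0.05 × 0.95 = 9.5 %. With an illustrative Bonferroni alpha of 0.05/3, 0.3 SD and 164 per arm, it is 59, 56, 51, 47 and 43 % over the same shares.

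**What an interaction test can do.** Its standard error in SD units is √(2/(n(1 − f)) + 2/(nf)). With n = 175 and f = 10 % this is √(2/157.5 + 2/17.5) = 0.356. Power for a between-type difference of 0.3 SD is then 13 %, and the difference detectable with 80 % power is 2.802 × 0.356 = 1.00 SD. For f = 20 % the figures are 20 % and 0.75 SD; for f = 30 %, 25 % and 0.65 SD.

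All of this treats the comparison as two means at 24 months. The planned covariate-adjusted longitudinal model would change the power somewhat. No corresponding calculation was made for IOP success.

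**The case against.** The strongest reply is that this is one sentence in a condensed article, and that a separate analysis plan may already contain an interaction test. The word used is stratified, which could also mean adjusted for type, and no decision rule is stated. The plan is otherwise sound here: one pre-specified baseline factor that is also a randomisation stratum. Not powering subgroups is normal practice.

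Part of this stands. Separate analysis is the natural reading under that heading, but it is not explicit. A reader might infer that the investigators will declare a difference between types by comparing p values; nothing in the article says so. A reader might also infer that discordant results are to be expected whatever the truth. The figures do not support that: discordance falls below half at 0.2 SD or less, at 0.5 SD once XFG reaches 20 %, and with the illustrative Bonferroni alpha at larger XFG shares. Nor does the sentence cover every outcome, since it names only HRQoL and clinical efficacy.

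The core remains. The article does not leave the subgroup method open. It names one, and that method does not answer whether the effect differs by type. On the alternative reading, adjustment for type, the sentence would provide no subgroup analysis at all.

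It is also fair to say that an interaction test has little power here and that a longitudinal model needs more than one extra term. Both bear on how the fix is worded, not on whether it is needed.

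**Conclusion.** The concern holds in a limited form. Followed as written and read naturally, the subgroup plan yields two within-type results and no estimate of the difference between them. At the design effect of 0.3 SD, 164 evaluable per arm, unadjusted two-sided 5 % and an assumed XFG share of 10-30 %, identical effects would give exactly one significant type in about 55-67 % of trials, and in 50 % at an even split. An interaction test would wrongly signal a difference in 5 %. The size rests on the assumed XFG share and on the true effect being near the design value.

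A reader might infer that the trial's main conclusion is at risk. It is not: the primary analysis uses all randomised patients and does not depend on the subgroup results.

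**What to change.** Replace the sentence under *Planned subgroup analyses* with a rule along these lines:
- For the HRQoL and clinical efficacy outcomes, fit the regression model (GEE/GLMM, logistic or Cox) on all patients with a treatment-by-glaucoma-type interaction. For longitudinal HRQoL, the quantity of interest is the treatment-by-type contrast at 24 months, which generally needs treatment-by-type-by-visit terms. The chi-square tests cannot carry this contrast, so the logistic model should.
- Report the interaction estimate with its 95 % CI, and the POAG and XFG effects with CIs from the same model.
- Base any claim that the types differ only on the interaction, and label it exploratory.
- State that a non-significant result within one type is not evidence of no effect in that type.

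The cost is a short change of text and a few model terms. Glaucoma type is already recorded and used in randomisation, and neither the design nor the sample size changes. The downside is low power: about 13-25 % for a 0.3 SD difference between types at 10-30 % XFG and 175 per arm. The interaction should therefore be read as an estimate with its CI, and a non-significant interaction should not be taken as proof that the types respond alike.

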### Sample size estimation

The sample size for the study is based on the primary outcome measure of HRQoL at 24 months post-treatment. Our hypothesis is that compared with topical medication, SLT treatment will have a significantly greater positive impact on HRQoL. Mean and standard deviations for the pilot data of GOAT and previous work with the Glau-QoL were used [36, 38]. To detect a 0.156 Logit difference (effect size of 0.3) on the Rasch-analysed GOAT and Glau-QoL at 80 % power with a 5 % level of significance, 175 patients will be needed in each group. Similarly, the mean and standard deviation values for the AQoL-7D were obtained from the literature [39, 47]. To detect a 0.7 difference (effect size of 0.3) on the AQoL-7D between the two groups at 24 months with 80 % power at 5 % level of significance; 176 patients will be needed for each group. Assuming an attrition rate of 15 % after 2 years, 193 patients will be enrolled in each group at baseline. Furthermore, for Aim 3, the study will also have 79 % power to detect a 10 % difference in ‘success rate’ of IOP (defined as ≥25 % reduction in baseline IOP) in the SLT group compared with topical medication using a two-sided log-rank test at the 5 % significance level.

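### Enrolling 193 per group does not cover the stated 15 % attrition: about 164 would remain, giving about 77 % power for the primary outcome instead of 80 %.

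*Protocol article*

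**What the plan says.** All figures below come from the section on sample size estimation in the protocol article unless another section is named.

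- The trial is sized on health-related quality of life at 24 months.
- For the two glaucoma-specific scales the target is: "To detect a 0.156 Logit difference (effect size of 0.3) on the Rasch-analysed GOAT and Glau-QoL at 80 % power". The result is that "175 patients will be needed in each group".
- For the AQoL-7D, also at an effect size of 0.3, the text reads: "with 80 % power at 5 % level of significance; 176 patients will be needed for each group".
- The step from evaluable to enrolled patients is one sentence: "Assuming an attrition rate of 15 % after 2 years, 193 patients will be enrolled in each group at baseline".
- The general statistical section fixes the test level: "All hypothesis testing will be performed at the 5 % two-sided significance level". The section on interventions fixes the allocation: "Patients will be randomised 1:1 to treatment with either SLT or topical ocular hypotensive therapy".

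**The concern.** The paragraph prints the required number, the expected loss and the enrolled number, so it can be checked without outside information. An enrolment of 193 is only 17 to 18 patients above the 176 or 175 required, while 15 % of 193 is about 29 patients. At least one of the three figures is therefore wrong: the attrition rate, the enrolment number or the 80 % power.

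What is at stake is the stated power for the primary outcome. The article's discussion itself notes that intensive interviewing may cause drop-out, so an attrition allowance that falls short of its own assumption is not a mere formality.

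**Working it through.** **Inputs.** Effect size 0.3, power 80 %, attrition 15 %, enrolled number 193 per group (sample size section). Two-sided 5 % (general statistical section). Allocation 1:1 (interventions section).

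**1. Reproduce the base number.**

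n per group = 2 × (1.960 + 0.842)² / 0.3² = 174.4, rounded up to 175 (normal approximation). The two-sample t-test gives 175.4, rounded up to 176. Both printed figures reproduce. They are numbers of patients with an outcome, before any allowance for loss.

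**2. Apply 15 % attrition.**

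| Method | From 175 | From 176 |
|---|---|---|
| Divide by (1 − 0.15) | 205.9 → 206 | 207.1 → 208 |
| Multiply by 1.15 (a common shortcut that is too small) | 201.3 → 202 | 202.4 → 203 |

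Neither method gives 193.

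**3. Find the loss that 193 does cover.**

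- 1 − 175/193 = 9.3 %
- 1 − 176/193 = 8.8 %

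The number 193 also equals 175 × 1.10 = 192.5 rounded up, so a 10 % mark-up may be its origin. The article does not say so.

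**4. Find the power at 193 enrolled with 15 % lost.**

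- Remaining per group: 193 × 0.85 = 164.05, so 164.
- Normal approximation: 0.3 × √(164/2) − 1.960 = 2.717 − 1.960 = 0.757, which gives power 77.5 %.
- Two-sample t-test: 77.3 %.
- Effect detectable at 80 % power: 0.3 × √(174.4/164) = 0.309, about 0.31.

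**5. Check the corrected number.**

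208 × 0.85 = 176.8, so at least 176 per group remain and the t-test power is 80.1 %. In total this is 416 patients against the 386 implied by 193 per group, a difference of 30.

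**The case against.** The strongest objection is that 77 % describes an unadjusted comparison of patients with 24-month data, whereas the primary analysis section plans covariate-adjusted repeated-measures models (GEE or GLMM) that can use partial follow-up. Both features may recover power. For example, if the covariates correlated 0.2 with the outcome (an assumption), the effective number would be 164/(1 − 0.04) = 170.8 and power about 79 %. At 0.3 (also an assumption) it would be 164/(1 − 0.09) = 180.2 and about 81 %. So the documents do not show that the trial's real power must be below 80 %.

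That limits the consequence but does not rescue the paragraph. The calculation is for 24-month quality of life, makes an explicit allowance for loss and takes no credit for adjustment or partial data. The primary analysis section also describes its intention-to-treat analysis as including those with 24-month questionnaire data. Nor is this a matter of an article condensing a longer protocol, since all three conflicting figures are printed.

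A reader might go further and infer that the IOP power is overstated in the same way. The article says "the study will also have 79 % power to detect a 10 % difference in" the IOP success rate by a log-rank test, and about 79 % does arise with all 193 per group at, for instance, 80 vs 90 % success (two proportions, 78.8 %). The documents do not support that inference. They give neither the reference success rate nor the number of patients behind the 79 %. With 164 per group a similar power arises at 83 vs 93 % (two proportions, 79.9 %) or 78 vs 88 % (log-rank with success as the event, Schoenfeld, 79.3 %). Across assumed rates, a 10-point difference with 164 per group has two-proportion power from 44 % (45 vs 55 %) to 86 % (85 vs 95 %, and likewise 5 vs 15 %). The figure can be neither reproduced nor refuted from the article, and the missing inputs may stand in the full protocol.

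The log-rank basis is not plainly at odds with the planned analysis either. The clinical efficacy section says "To assess clinical efficacy (IOP reduction success), Chi square tests will be used", but it also plans Kaplan-Meier and Cox analyses of IOP success.

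**Conclusion.** The point holds for the primary outcome. The required number is right, but the enrolled number does not follow from it at 15 % attrition: 206 to 208 per group would be needed, and 193 tolerates about 9 %. At 15 % loss, power under the section's own calculation is about 77 %, a shortfall of just under 3 percentage points, and the detectable effect moves from 0.30 to about 0.31.

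This rests only on printed inputs and on reading attrition as the share of enrolled patients without a 24-month outcome. It is a clear but modest error in a stated sample size. It does not show that the trial is seriously underpowered, and no conclusion about the 79 % for IOP follows from it.

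**What to change.** Restate the paragraph so that base number, attrition and enrolment agree, in one of two ways:

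- **Keep 193 per group.** State that 15 % attrition leaves 164 per group and about 77 % power at an effect size of 0.3, and that 80 % holds only up to about 9 % attrition. This costs one reworded paragraph and a slightly less favourable power statement, with no extra patients.
- **Keep 80 % power at 15 % attrition.** Give 208 per group, the number that serves all three instruments. This costs 15 more patients per group, 30 in total.

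If the sponsor wishes to rely on covariate adjustment or partial follow-up to close the gap, the paragraph should say so and state the assumed correlation.

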### Side-effects reporting and quantification

Information about transient ocular discomfort and pain; mild uveitis; IOP spikes; the presence/absence and severity of ocular surface disease (OSD) signs and symptoms; anterior chamber reaction (cells and flare 1 hour post-laser) and any other sight threatening and non-sight threatening adverse events will be collected. IOP spikes are defined as an elevation >30 mmHg or >30 % increase within the first 4 weeks post-treatment. The presence or absence of OSD signs and symptoms will be obtained from the results of the biomicroscopy, in particular, concerning whether any hyperaemia and/or superficial punctate epitheliopathy is present and the extent of this and also from the responses provided by participants to the OSD Index Questionnaire. This questionnaire was developed by Allergan, Inc’s Outcomes Research Group to provide a rapid assessment of the severity of symptoms of OSD and their impact on vision-related function and has been validated in English speaking subjects [48]. We obtained permission to use this questionnaire.

An adverse event (AE) is defined as any untoward medical occurrence in a patient administered therapy that does not necessarily have a causal relationship with this treatment. An AE can therefore also be any unfavourable and unintended sign (including an abnormal laboratory finding), symptom, or disease temporally associated with the use of a therapy, whether or not it is related to the therapy itself. Any AE will be recorded on the appropriate case report form. It will be graded by an Investigator at each site for severity and relationship to study treatment. An AE reporting system will be implemented to ascertain the occurrence of both anticipated and unanticipated AEs. When indicated, patients suffering AEs will be referred for appropriate ophthalmic or medical care. Information regarding AEs (including incidence, duration, seriousness, severity, relationship to treatment, and action taken) will be recorded throughout the 2 years of the study. If AEs occur, the first concern will be the study participant’s safety. To determine the relationship (if any) between an AE and the study intervention, a causal relationship is deemed present if a determination is made that there is a reasonable possibility that the AE may have been caused by the intervention.

Safety data will be compiled every 6 months by the unmasked investigator and coordinator and submitted to the Study Project Manager, who will, in turn, forward it to the Data Safety Monitoring Committee (DSMC) for review at 6-month intervals. All AEs that are therapy related and unexpected will also be reported to the site’s Human Research Ethics Committee (HREC).

A serious AE (SAE) will be defined as any AE that results in any of the following outcomes: death, a life-threatening AE, inpatient hospitalization or prolongation of existing hospitalization, a persistent or significant disability/incapacity, or a congenital anomaly/birth defect. Important medical events that may not result in death, be life threatening, or require hospitalization may be considered SAE events when, based upon appropriate medical judgment, they may jeopardise the patient and may require medical or surgical intervention to prevent one of the outcomes listed in this definition. Any SAE occurring during the study period and for at least 28 days after the last administration of therapy will be reported as soon as possible to the Study Project manager and also recorded on the appropriate case report forms. All participants with a SAE will be followed up and the outcomes reported. For other SAEs, the governing HREC will be notified as required by their regulations. The investigator will supply the Project Manager and the HREC with any additional requested information (for example, autopsy reports and terminal medical reports).

